#### Cost-Effectiveness

To compare the cost-effectiveness of the 2 telemedicine approaches, a bottom-up approach will be used, a method for the assessment of each resource required to provide health care and assigning the related costs accordingly [21,22]. For both the supervised and follow-up groups, the mean performance outcome for each of the 5 preintervention evaluation tests will be computed. These means are then compared within their group (supervised or follow-up) to a mean for the same 5 postintervention evaluations, determining the mean outcome (increase or decrease) for each of the 5 tests. These mean outcomes will then be compared to the total cost of each telemedicine approach to determine the cost (on a per-unit basis) of the health outcome. Doing so allows for the assessment of not only which telemedicine approach has a higher cost overall, but most importantly, the per-unit cost of the health outcome for the supervised and follow-up groups. This provides a more accurate comparison, with respect to financial costs, of the 2 methods.

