#### Cost

To determine the cost comparison between the 2 groups, the number of hours spent by the kinesiologist delivering the exercise intervention to the supervised group will be recorded and compared to the number of hours spent with participants in the follow-up group. The kinesiologist will be paid a rate which is commensurate with their previous experience as well as a wage that aligns with the rate of pay for a kinesiologist in the market in which this study is conducted. The equipment costs (Microsoft Teams, Polar heart rate monitor, resistance band, and weighted exercise ball) will be reported and included in the calculations. When drawing cost comparisons for the 2 approaches, the supervised approach is a group approach, whereas the follow-up approach is an individualized approach. Therefore, a direct comparison between the 2 approaches presents a challenge. Nevertheless, to mitigate the difference in group and individualized approaches, the cost comparison for both the supervised and follow-up groups will be computed and presented as a cost per participant.

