### Statistical Analysis

As this is a feasibility study, the testing procedure will be assessed rather than only focusing on the potential outcomes of the intervention. To determine the optimal clinical practice of telemedicine for an exercise intervention, recruitment, adherence, and completion rates of 2 randomized groups (supervised and follow-up approaches) will be investigated. Descriptive statistics will be presented as means and SDs. Based on previous research on home-based exercise interventions [23], the adherence rate will be assessed with a set threshold of 80%. A Wilcoxon rank sum test will be used to evaluate the adherence rate and compare both telemedicine approaches. Whereas both recruitment and completion rates will be compared using descriptive statistics and assessed with a set threshold of 50%. To measure the change in outcome parameters of participants’ muscle strength and cardiopulmonary fitness, pre- and postintervention evaluation results will be assessed with a Friedman ANOVA. A Kruskal-Wallis test will be used to determine the differences in outcome parameter changes between the 2 groups (supervised and follow-up groups).

To assess the cost-effectiveness of the 2 telemedicine approaches, a cost-effectiveness plane and an incremental cost-effectiveness ratio will be computed. The incremental cost and incremental effect will be plotted on a cost-effectiveness plane, where the horizontal axis will represent the incremental cost and the vertical axis will represent the incremental effect [24,25]. The costs and clinical outcomes for both telemedicine groups will be plotted on the plane, which will visually demonstrate the additional cost per unit of health gain for each telemedicine approach. To calculate the incremental cost-effectiveness ratio, the difference in costs will be divided by the difference in mean performance outcomes between the supervised and follow-up groups.

Finally, as OI is classified as a rare disorder [1], analyses will be carried out with a significance level (α) of 0.10 [26]. Statistical analyses will be conducted using the statistical analysis software SPSS, version 25 (SPSS Inc).

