**Kinesiologist**
Evaluations2 hours (preintervention evaluation)+2 hours (postintervention evaluation)×6 participants=24 hoursInterventionEstimated time required for the supervised approach
(8 hours [month 1]+12 hours [month 2]+18 hours [month 3])×2 (number of groups)=76 hours
24 hours (evaluations)+76 hours (intervention)=100 hours
Total: 100 hours (total hours)×CAD $27 (US $20) (hourly rate)=CAD $2700 (US $2006)
Estimated time required for the follow-up approach
(2 hours [month 1]+2 hours [month 2]+2 hours [month 3])×6 (number of participants)=36 hours
24 hours (evaluations)+36 hours (intervention)=60 hours
Total: 60 hours (total hours)×CAD $27 (US $20) (hourly rate)=CAD $1620 (US $1204)

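### Cost per unit of each arm's own gain can rank the two approaches on costs they share; the incremental comparison should take precedence, on one per-participant cost scale without evaluation hours

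*Protocol article*

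**What the plan says.** Cost-effectiveness is part of the first objective. The article describes two measures.

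- **Per-arm ratio (Cost-Effectiveness section).** Pre and post means are compared within each arm, "determining the mean outcome (increase or decrease) for each of the 5 tests". Then: "These mean outcomes will then be compared to the total cost of each telemedicine approach to determine the cost (on a per-unit basis"). The section singles out this per-arm figure as the result that matters most and as giving the more accurate financial comparison.
- **Incremental ratio (Statistical Analysis section).** A cost-effectiveness plane is planned together with a ratio in which "the difference in costs will be divided by the difference in mean performance outcomes between the supervised and follow-up groups".

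On what is costed, the Cost section says that "the number of hours spent by the kinesiologist delivering the exercise intervention to the supervised group will be recorded" and compared with hours spent with follow-up participants. Equipment and Microsoft Teams are included. The comparison for both arms "will be computed and presented as a cost per participant".

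The itemised estimate (Textbox 1) counts pre- and postintervention evaluation time as well: "24 hours (evaluations)+76 hours (intervention)=100 hours" for the supervised arm and "24 hours (evaluations)+36 hours (intervention)=60 hours" for the follow-up arm. Table 2 gives totals per group and per participant.

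**The concern.** Three things do not fit together.

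1. A per-arm ratio of cost to gain compares each approach with spending nothing and gaining nothing. The choice here is between two active approaches, so only the difference in cost and the difference in effect bear on it. Anything both arms pay equally still enters the per-arm ratio and can decide its ranking.
2. The evaluations supply the study's outcome data. The Cost section describes the supervised-arm hours as delivery hours, yet the estimate includes evaluation time.
3. The effect is a mean per participant. The cost set against it is called the total for the approach in one section and a per-participant cost in another, and the Statistical Analysis section gives no scale.

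At stake is which approach is reported as more cost-effective, and at how many dollars per unit. The two planned measures can suggest different answers, and the text gives more weight to the weaker one.

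**Working it through.** **Inputs** (Textbox 1 and Table 2): CAD 27 per hour; evaluation 24 h per arm; intervention 76 h supervised and 36 h follow-up; equipment CAD 274.28 per participant; Teams 4 × 18.40 = CAD 73.60 per arm; 6 participants per arm.

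**Reproducing the stated totals**

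- Supervised: 100 × 27 + 6 × 274.28 + 73.60 = 2700 + 1645.68 + 73.60 = 4419.28 (stated 4420); ÷ 6 = 736.55 (stated 736).
- Follow-up: 60 × 27 + 1645.68 + 73.60 = 1620 + 1719.28 = 3339.28 (stated 3340); ÷ 6 = 556.55 (stated 556).

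Table 2 reproduces to rounding.

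**Dependence on shared costs.** With cost C and mean gain E (both gains positive), supervision has the lower cost per unit when E_sup / E_fu > C_sup / C_fu.

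| Costs counted, per participant | Supervised | Follow-up | Break-even gain ratio | Difference |
|---|---|---|---|---|
| All in Table 2 | 736.55 | 556.55 | 1.32 | 180 |
| Without evaluation hours (24 × 27 = 648; 648 ÷ 6 = 108) | 628.55 | 448.55 | 1.40 | 180 |

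The article gives no expected gains, so the next figures are illustrative assumptions. Take mean gains of 5.5 and 4 repetitions (ratio 1.375).

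- All costs: 736.55 / 5.5 = 133.9 against 556.55 / 4 = 139.1, so supervision ranks better.
- Without evaluation hours: 628.55 / 5.5 = 114.3 against 448.55 / 4 = 112.1, so follow-up ranks better.
- Incremental ratio in both cases: 180 / 1.5 = CAD 120 per repetition.

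**Sign.** Table 1 records the heel-rise test in seconds, and its description asks for a fixed number of rises at top speed, so a better result is a shorter time. Assume mean times fall by 6 s and 4 s. The ratios are 736.55 / (−6) = −122.8 and 556.55 / (−4) = −139.1. Follow-up now has the lower signed value. The same sizes of gain in repetitions give 122.8 against 139.1, which favours supervision. As a mean change approaches zero, the ratio grows without limit.

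**Scale.** Incremental cost is 4419.28 − 3339.28 = 1080 per group, or 1080 ÷ 6 = 180 per participant. With assumed gains of 6 and 4 repetitions, the incremental ratio is 1080 / 2 = 540 or 180 / 2 = 90 per repetition. The per-arm ratios are 736.5 against 834.8 on group totals and 122.8 against 139.1 per participant. The factor of 6 is common to both arms, so the order is unchanged.

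**The case against.** Much can be said for the plan as written.

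- **The better measure is already there.** The incremental ratio and the plane are planned, and shared costs cancel in them. This stands. The shared-cost problem is confined to the per-arm ratio, and what needs changing is the weight given to it.
- **A six-fold scaling error is not established.** A reader might infer one from the words about total cost. Textbox 1 does use its per-approach label for whole-group amounts, but the Cost section commits to per-participant figures and Table 2 supplies them. The scale is inconsistent, not shown to be wrong.
- **Larger swings are not supported.** Dropping equipment and Teams as well leaves delivery hours only (2052 against 972) and a break-even of 2.11. The Cost section properly counts those items as resources, so this is no measure of the error. Only the evaluation hours are in question, and they move the break-even from 1.40 to 1.32.
- **The evaluation-hours conflict is partial.** The wording for the follow-up arm is looser than for the supervised arm, and Textbox 1 itemises the two kinds of hours, so either total can be recovered. The conflict with the supervised-arm wording remains.
- **Incremental ratios also misbehave** when the difference in effect is near zero, which is plausible with 6 per arm. This is true, and it is a reason to report the incremental cost and effect as a pair on the plane. It does not rescue the per-arm ratio, which is additionally moved by shared costs.
- **This is a 12-person pilot** with no stated adoption rule and acknowledged limits. That tempers the severity. Cost-effectiveness is nevertheless a main objective.

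**Conclusion.** The concern holds in limited form and should be fixed. The per-arm cost per unit is not a sound basis for saying which approach is more cost-effective. Its ranking depends on costs equal in both arms, and it cannot be interpreted for zero or negative changes. Including the evaluation hours (CAD 648 per arm) reverses that ranking only if the ratio of gains falls between 1.32 and 1.40. The incremental cost stays at CAD 180 per participant throughout. The unfixed scale leaves the incremental numerator at CAD 1080 or CAD 180. With 6 per arm this changes reported dollars, not the ranking.

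It does not follow that the whole cost-effectiveness analysis is invalid, because the incremental analysis in the Statistical Analysis section is free of the shared-cost problem.

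The figures rest on the article's anticipated costs, with 6 participants costed per arm. All mean changes used are illustrative.

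**What to change.** 1. State that every ratio, per-arm or incremental, uses cost per randomised participant.
2. Report the evaluation hours on a separate line and exclude them from intervention cost. Keep equipment and Teams. On the current estimates the per-participant totals become about CAD 629 and CAD 449.
3. Base the cost-effectiveness conclusion on the incremental cost and incremental effect already planned, shown as a pair on the plane.
4. Drop the per-arm cost per unit as a decision measure. Tabulate per-arm cost and mean change side by side for each test.
5. State each test's direction of improvement, so that a fall in heel-rise time counts as a gain.

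The cost is a rewording of the Cost and Cost-Effectiveness sections, one sentence in Statistical Analysis and a revised Table 2. No new data are needed.

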### Statistical Analysis

As this is a feasibility study, the testing procedure will be assessed rather than only focusing on the potential outcomes of the intervention. To determine the optimal clinical practice of telemedicine for an exercise intervention, recruitment, adherence, and completion rates of 2 randomized groups (supervised and follow-up approaches) will be investigated. Descriptive statistics will be presented as means and SDs. Based on previous research on home-based exercise interventions [23], the adherence rate will be assessed with a set threshold of 80%. A Wilcoxon rank sum test will be used to evaluate the adherence rate and compare both telemedicine approaches. Whereas both recruitment and completion rates will be compared using descriptive statistics and assessed with a set threshold of 50%. To measure the change in outcome parameters of participants’ muscle strength and cardiopulmonary fitness, pre- and postintervention evaluation results will be assessed with a Friedman ANOVA. A Kruskal-Wallis test will be used to determine the differences in outcome parameter changes between the 2 groups (supervised and follow-up groups).

To assess the cost-effectiveness of the 2 telemedicine approaches, a cost-effectiveness plane and an incremental cost-effectiveness ratio will be computed. The incremental cost and incremental effect will be plotted on a cost-effectiveness plane, where the horizontal axis will represent the incremental cost and the vertical axis will represent the incremental effect [24,25]. The costs and clinical outcomes for both telemedicine groups will be plotted on the plane, which will visually demonstrate the additional cost per unit of health gain for each telemedicine approach. To calculate the incremental cost-effectiveness ratio, the difference in costs will be divided by the difference in mean performance outcomes between the supervised and follow-up groups.

Finally, as OI is classified as a rare disorder [1], analyses will be carried out with a significance level (α) of 0.10 [26]. Statistical analyses will be conducted using the statistical analysis software SPSS, version 25 (SPSS Inc).

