Telemedicine is a method for the remote delivery of professional health services at a distance by linking clinicians and patients through information technology [10,11]. Lambert et al [12] used a telemedicine approach for the delivery of a 16-week home exercise program for pediatric acute lymphoblastic leukemia survivors. This supervised telemedicine approach was shown to be feasible, as the results demonstrated a mean adherence rate of 89% and a completion rate of 75% [12]. In contrast, Gagnon et al [13] used a follow-up telemedicine approach for the delivery of a 12-week home exercise program for youth with arthrogryposis multiplex congenita, where clinicians conducted follow-ups with study participants every 3 weeks. The results showed a 68% adherence rate and a 64% completion rate, which was sufficient for most study participants to achieve their goals [13]. As the recent literature demonstrates, the follow-up approach may be less effective as it led to a lower completion rate [12,13]. However, additional clinician time cost associated with the supervised approach may exceed the increase in benefits associated with constant supervision.

There remains a gap in the literature with respect to the comparison between supervised and follow-up telemedicine approaches and the associated cost-effectiveness of both approaches. Hence, the aim of this study is to evaluate the feasibility and cost-effectiveness of 2 telemedicine approaches (supervised vs follow-up) for the delivery of a home exercise program. The secondary aim of the study is to investigate the effectiveness of the home-based exercise program on muscle function and cardiopulmonary fitness in youth with OI type I. Given the aims of this study, it is hypothesized that participants in the supervised group will have higher adherence and completion rates compared to the follow-up group, which will be further associated with greater increases in muscle strength and cardiopulmonary fitness from the exercise intervention. However, the additional intervention delivery time required for the supervised group may make it less cost-effective compared to the follow-up approach.

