### Recruitment

A total of 12 patients with OI type I will be recruited at a tertiary orthopedic hospital. Given that this study will be conducted remotely, patients who meet the study eligibility criteria will be contacted by the study coordinator over the phone. Those who are interested in participating will receive a follow-up email from the study coordinator with the appropriate consent or assent form, providing them with more information regarding their participation. Based on participant’s preference, consent or assent forms will be either emailed or mailed to their place of residence. To ensure privacy, all emails from the study coordinator will be sent encrypted. Study participants will be randomized into either (1) the supervised group or (2) the follow-up group. Study personnel will produce a block randomization list using a random number generating software, which will be sent to the principal investigator. Each randomized number will be written on piece of paper and placed in an envelope. Once a study participant is enrolled, a hospital employee who is not involved in the study will select one of the envelopes and deliver it to the study personnel, who will assign the study participant to the specified group.

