### Measurement

#### Feasibility

In determining the feasibility of the telemedicine approaches for the delivery of an exercise intervention, recruitment, adherence, and completion rates will be measured. Recruitment rate will be calculated by dividing the study sample by the total number of contacted potential participants [19]. Adherence rate is defined as the percentage of the exercise intervention sessions completed per participant [20]. To monitor participants’ adherence to the exercise intervention, data exported from the activity monitor (Polar watch) will be recorded by study personnel on an activity log for all participants in both groups. Finally, completion rate is defined as the number of participants that completed the exercise intervention as a percentage of the overall number of participants that began the intervention [20].

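### Recruitment is fixed before randomisation and cannot be compared between the two groups, and completion should be computed on all randomised participants, not only on those who began.

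*Protocol article*

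**What the plan says.** The Statistical Analysis section sets out to find the better way of delivering the programme and states that "recruitment, adherence, and completion rates of 2 randomized groups (supervised and follow-up approaches) will be investigated". It then says that "both recruitment and completion rates will be compared using descriptive statistics and assessed with a set threshold of 50" percent. It does not say whether exactly 50% meets the threshold.

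The Feasibility section under Measurement defines the two rates. For the first, "Recruitment rate will be calculated by dividing the study sample by the total number of contacted potential participants". Completion is the number who finished the programme, "as a percentage of the overall number of participants that began the intervention".

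The Recruitment section gives the order of events. First, "patients who meet the study eligibility criteria will be contacted by the study coordinator over the phone"; consent or assent forms follow. Only then comes allocation: "Once a study participant is enrolled, a hospital employee who is not involved in the study will select one of the envelopes". The Overview under Evaluations and Intervention places two weeks of evaluations before the 12-week programme.

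The Introduction cites earlier work on each approach: "a mean adherence rate of 89% and a completion rate of 75" percent for a supervised programme, and a "68% adherence rate and a 64% completion rate" for a follow-up programme.

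**The concern.** A feasibility measure can inform the choice between two randomised approaches only if it is observed after allocation and can differ by group. Recruitment meets neither condition, yet it is listed among the rates of the two groups and is to be compared. If an analyst does produce a figure per group, it will reflect the allocation ratio and nothing about either approach.

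Completion meets both conditions, but its denominator is itself settled after allocation. A family that learns its group and then does not start has given direct evidence about the acceptability of that format, and the definition removes it. The two formats ask for different things: live group sessions in one, self-timed exercise in the other. Non-starting could therefore differ between them, and the comparison would then be between selected subsets of the randomised groups. What is at stake is the primary aim, since the Abstract promises to determine the most feasible approach.

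**Working it through.** The article gives no sample-size or operating-characteristic figure for these criteria, so there is no stated figure to reproduce.

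**Inputs.** 12 participants, 6 per group (Abstract). Threshold 50% (Statistical Analysis). Cited completion 75% supervised and 64% follow-up (Introduction). Definitions and sequence as quoted above.

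**1. Recruitment.** Rate = study sample / number contacted = 12/C, where C is everyone contacted before any allocation.
- Numerator and denominator are each a single number for the trial. The rate meets 50% when 12/C ≥ 0.50, that is, when C ≤ 24.
- A forced split gives 6/C in each group. As C is at least 12, this is at most 6/12 = 50%. With C = 24, the trial rate is 12/24 = 50% but each split figure is 6/24 = 25%. The two split figures are always equal under 6:6 allocation, so they carry no information about the approaches.

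**2. Completion denominator.** Let s be the non-starters among 6 randomised and c the completers. The rate as defined is c/(6 − s); on all randomised it is c/6. The article gives no value for s, so these cases are illustrations.

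| s | c | as defined | all randomised |
|---|---|---|---|
| 0 | 3 | 3/6 = 50% | 3/6 = 50% |
| 1 | 3 | 3/5 = 60% | 3/6 = 50% |
| 1 | 5 | 5/5 = 100% | 5/6 = 83% |
| 2 | 2 | 2/4 = 50% | 2/6 = 33% |
| 3 | 2 | 2/3 = 67% | 2/6 = 33% |

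If the threshold means at least 50%, the pass or fail result changes only with two or more non-starters in a group. If it means above 50%, one is enough (third completer in the second row: 60% passes, 50% does not). Under either rule, a single non-starter shifts the descriptive comparison as long as someone in that group completes.

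**3. What the 50% threshold can separate.** Take X ~ Binomial(6, p), independent groups, everyone starting, and the cited rates holding here.
- At least 50% (X ≥ 3), p = 0.75: 1 − (0.0002 + 0.0044 + 0.0330) = 0.962.
- At least 50%, p = 0.64: 1 − (0.0022 + 0.0232 + 0.1032) = 0.871.
- Both pass: 0.962 × 0.871 = 0.84. Exactly one passes: 0.124 + 0.033 = 0.16.
- Above 50% (X ≥ 4): 0.831 and 0.627. Both pass: 0.52. Exactly one passes: 0.310 + 0.106 = 0.42.

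**4. Descriptive comparison of completion.** Under the same assumptions, the supervised group has the higher observed rate with probability 0.543, the groups tie with 0.227, and the follow-up group is higher with 0.230.

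**The case against.** On recruitment, the definition in the Feasibility section already yields one trial-wide figure. The hypotheses in the Introduction and Discussion concern adherence and completion only, and no between-group test of recruitment is planned. The Statistical Analysis sentence may be no more than loose wording. That limits the consequence, but the sentence still promises a comparison that the definition and the sequence of enrolment rule out.

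On the denominator, the definition is stated openly and taken from a cited source, non-starting is hypothetical here, and under a rule of at least 50% one non-starter never changes the result. The Limitations section also lets supervised participants make up missed sessions in their own time, which softens the burden of live sessions. All of this stands. It makes the likely effect small; it does not make the exclusion harmless in a group of 6.

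A reader might go further and infer that completion cannot identify the more feasible approach at all, or that a 50% threshold is an error because it lies below both cited rates. The document supports neither. Completion varies by group and is compared descriptively as well as against the threshold. Its weak discrimination owes much to 6 per group, and the Limitations section acknowledges the small sample. A minimum for feasibility may properly sit below what is hoped for, and the cited rates come from other conditions, one of them from a 16-week programme.

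**Conclusion.** The point holds for recruitment without qualification: no group-specific rate exists, so it cannot contribute to choosing between the approaches. It also holds for the completion denominator, as a post-randomisation exclusion from a main feasibility measure. The size of that second effect is unknown. One non-starter with 5 completers moves a group from 83% to 100%, and two non-starters with 2 completers move it from 33% to 50%. The window for such withdrawals is inferred from allocation at enrolment and the two evaluation weeks that follow; the article does not say exactly when families learn their group.

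The 50% threshold is acceptable as a minimum. It should not be used to rank the approaches, because at the cited rates it leaves both groups passing with probability about 0.84, or 0.52 if 50% must be exceeded. Those figures rest on the cited rates applying to this population, on independent groups and on all 6 starting. Raising the threshold to the cited 64% (at least 4 of 6) is not a clear improvement: a group whose true rate is 64% would then fail with probability 1 − 0.627 = 0.37.

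**What to change.** - Report recruitment once, for the whole trial, against the 50% threshold, and remove it from the rates compared between the two groups.
- Define completion per group as completers divided by all participants randomised to that group. Keep the rate among those who began as a supplementary figure, and give the number of non-starters per group.
- State that the 50% threshold is a minimum for feasibility and does not rank the approaches, and say whether exactly 50% meets it.

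The cost is a change of wording in the Feasibility and Statistical Analysis sections, with no new data or participants. The main completion figure can only stay the same or fall, so it may look slightly less favourable. The supplementary rate preserves the present definition for anyone who needs it.

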**Methods:**

Patients with OI type I (the mildest form of OI; n=12, aged 12-16 years) from a pediatric orthopedic tertiary hospital will be randomized to receive a 12-week remote exercise intervention in either (1) a supervised group (n=6), monitored every session, or (2) a follow-up group (n=6), receiving monthly progress update appointments. Participants will undergo the following pre- and postintervention evaluations: sit-to-stand test, push-up test, sit-up test, single-legged balance test, and a heel-rise test. Both groups will be given the same 12-week exercise regimen, which includes cardiovascular, resistance, and flexibility training. For each exercise training session involving the supervised group, a kinesiologist will provide instructions to participants through live video sessions using a teleconferencing application. On the other hand, the follow-up group will discuss their progress with the kinesiologist every 4 weeks over a teleconferencing video call. Feasibility will be assessed by recruitment, adherence, and completion rates. A cost-effectiveness analysis of both approaches will be computed. Changes in muscle function and cardiopulmonary fitness will be examined between the 2 groups, pre- and postintervention.

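### The between-arm comparison and the ICER use change scores without adjusting for baseline, so with six per arm a chance difference in starting level shifts the estimated effect

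*Protocol article*

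**What the plan says.** All references are to the protocol article.

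- **Between-arm test** (Statistical Analysis): "A Kruskal-Wallis test will be used to determine the differences in outcome parameter changes between the 2 groups". With two groups this is equivalent to a two-sided rank-sum test on the pre-to-post changes.
- **Pre-post test** (Statistical Analysis): "pre- and postintervention evaluation results will be assessed with a Friedman ANOVA". No baseline covariate is named for either test.
- **Significance level** (Statistical Analysis): "analyses will be carried out with a significance level (α) of 0.10". Sidedness is not stated; two-sided is assumed here.
- **Size and allocation** (Recruitment; Abstract, Methods): "A total of 12 patients with OI type I will be recruited at a tertiary orthopedic hospital", split into "a supervised group (n=6), monitored every session, or (2) a follow-up group (n=6), receiving monthly progress update appointments".
- **Randomisation** (Recruitment): "Study personnel will produce a block randomization list using a random number generating software". No stratification or baseline balancing is described.
- **Effect side of the ICER** (Cost-Effectiveness): in each arm "the mean performance outcome for each of the 5 preintervention evaluation tests will be computed", and the post-test means are then compared with these to give a mean change per test. Statistical Analysis divides the cost difference by the between-arm difference in mean performance outcome, which I read as this mean change.

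**The concern.** Baseline is measured for every performance test, but it enters the between-arm comparison only by subtraction. Unless r is close to 1, participants who start low tend to gain more than those who start high, through regression to the mean. The 45-second cap on the balance test strengthens this, because a participant near the cap has little room to improve.

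With six per arm and nothing described that balances starting level, a sizeable chance difference at baseline is likely, and part of it passes into the comparison of changes. For the Kruskal-Wallis test this affects a secondary aim. The ICER belongs to the main aim of the study and uses the same contrast as a point estimate, so the imbalance enters it directly.

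**Working it through.** The article gives no power, effect size, SD or pre-post correlation, so there is no figure of its own to reproduce. The correlation r is an assumption throughout, shown over a range. Pre and post variances are taken as equal, and outcomes as bivariate normal in the simulations.

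**1. Validity of the planned test.** Enumerating all 924 rank allocations of 6 vs 6, Kruskal-Wallis at 0.10 has exact size 0.093. It holds its level.

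**2. Expected baseline imbalance.** The SD of the difference in baseline means is √(1/6 + 1/6) = 0.58 baseline SD. The expected absolute value is 0.58 × √(2/π) = 0.46 SD. The chance of at least 0.5 SD is 39%, and of at least 1 SD 8%.

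**3. Shift in the change contrast.** Given a baseline difference D, the expected between-arm difference in change moves by (r − 1) × D. Null rejection rates below are for simulated trials with |D| of at least 0.58 SD.

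| r | Shift per SD of D | Shift at D = 0.46 | Kruskal-Wallis on change | Baseline-adjusted linear model |
|---|---|---|---|---|
| 0.5 | −0.50 | −0.23 | 14–15% | about 10% |
| 0.7 | −0.30 | −0.14 | 12% | about 10% |
| 0.8 | −0.20 | −0.09 | 11% | about 10% |
| 0.9 | −0.10 | −0.05 | 10% | about 10% |

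**4. Effect on the ICER (illustration).** The estimated cost difference in Table 2 is 736 − 556 = CAD 180 per participant. Assume a true difference in change of 0.5 SD and r = 0.5. With no imbalance the ICER is 180 / 0.5 = CAD 360 per SD. An imbalance of 0.58 SD shifts the effect by 0.5 × 0.58 = 0.29, giving 180 / 0.79 = CAD 228 or 180 / 0.21 = CAD 857, depending on which arm starts lower.

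**5. Precision.** The variance of the adjusted difference relative to the change-score difference is [(1 + r)/2] × [1 + 1/(N − 4)]. At N = 12 the second factor is 1.125, so the ratio is 0.84 at r = 0.5, 0.96 at 0.7, 1.01 at 0.8 and 1.07 at 0.9. Break-even is at r = 2/1.125 − 1 = 0.78.

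**6. Power.** 6 vs 6, alpha 0.10, true difference of 1 SD of the post-test value:

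| r | Kruskal-Wallis on change | Baseline-adjusted re-randomisation test |
|---|---|---|
| 0.5 | 46% | 55% |
| 0.7 | 62% | 68% |
| 0.8 | 78% | 81% |
| 0.9 | 96% | 96% |

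This comparison changes two things at once: it leaves ranks and it adjusts for baseline. A separate run with an unadjusted permutation test on raw change in the middle gave, for Kruskal-Wallis, raw-change permutation and adjusted test in turn, 46 / 49 / 55% at r = 0.5, 64 / 68 / 69% at 0.7, 80 / 83 / 82% at 0.8 and 96 / 98 / 96% at 0.9. Runs differ by up to about 2 points. Leaving ranks accounts for 3 to 4 points at r = 0.5 to 0.8. Baseline itself adds about 6 points at r = 0.5, 1 to 2 at 0.7 and nothing from about 0.8.

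**7. Fewer completers.** The Introduction cites completion of 75% and 64% in comparable programmes, that is 9 or 7.7 of 12. If about 4 per arm have post-tests (an assumption), raw-change permutation vs the adjusted test gives 31 vs 32% at r = 0.5, 38 vs 38% at 0.6, 45 vs 43% at 0.7 and 58 vs 54% at 0.8. The power gain has gone.

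**The case against.** A reader might infer three stronger criticisms, and the article supports none of them.

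- **That the plan ignores baseline.** It does not. A change score subtracts each participant's baseline, and the Cost-Effectiveness section computes the pre-test means. Only adjustment for the remaining dependence is absent.
- **That the planned test is biased or invalid.** It is not. Averaged over randomisations its size is 0.093, and the shift is as likely to favour either arm. The problem exists only given the imbalance that occurs.
- **That power is necessarily lost.** This depends on a correlation that the article does not report, and part of the apparent gain comes from leaving ranks.

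Further points deserve weight. The outcomes include repetition counts, a time capped at 45 seconds and a 0–5 score, so ranks are defensible at this size and the normal simulations flatter a linear model. Rank ANCOVA, which would keep the nonparametric approach, is no better than the planned test at r = 0.7 (44 vs 45%) and worse at 0.9 (35 vs 45%), for a difference of 1 SD of the change score. The plan is not without effect estimates either, since it reports means, SDs and mean changes. The performance comparison is a secondary aim of a pilot whose Limitations section already doubts that 12 participants allow strong conclusions.

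All of this stands, and it limits the point to a modest one. It does not remove the conditional shift: the trial will have one realised allocation, and the ICER uses the contrast as a point estimate.

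**Conclusion.** The concern holds in a limited form. The article fixes a between-arm comparison and an ICER effect that use unadjusted changes. With 6 per arm and no stratification described, the expected absolute baseline difference is 0.46 SD. At that imbalance the contrast moves by about 0.23 SD at r = 0.5, 0.14 at 0.7 and 0.09 at 0.8, in favour of the arm that starts lower. The main consequence is for the ICER, where a moderate effect in the denominator makes the ratio sensitive to a shift of this size.

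The power argument is secondary and conditional: about 9 points at r = 0.5 and 6 at r = 0.7 against an adjusted re-randomisation test, of which 3 to 4 come from leaving ranks. Baseline itself contributes nothing from about r = 0.8, or if only about 4 per arm have post-tests. These figures rest on assumed values of r, equal variances and normal outcomes.

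**What to change.** For each performance test, fit the post-test value on baseline and arm, and report the adjusted between-arm difference with a 90% CI, which matches the planned alpha of 0.10. Take the p-value by re-randomisation over the allocations that the block list permits. The article does not give the block size: blocks of 2 give 2⁶ = 64 allocations, blocks of 4 give 6³ = 216, and an unrestricted 6 vs 6 split gives 924. The actual scheme should therefore be stated and used. Put the adjusted difference in the denominator of the ICER, and keep the Kruskal-Wallis test on change alongside it.

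The cost is analysis wording and a short script; no new data are needed. One degree of freedom is used, with no gain in precision, or a slight loss, if r is about 0.8 or higher or if few participants complete. For capped or coarse outcomes the linear adjustment is only approximate, which is a further reason to keep the rank test beside it.
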